# Optimization of Preemptive Therapy for Cytomegalovirus Infections With Valganciclovir Based on Therapeutic Drug Monitoring: Protocol for a Phase II, Single-Center, Single-Arm Trial

**DOI:** 10.2196/72549

**Published:** 2025-06-24

**Keywords:** valganciclovir, ganciclovir, cytomegalovirus, therapeutic drug monitoring, preemptive therapy, dried blood spots

## Abstract

**Background:**

Valganciclovir (VGCV) is the first-line drug for preemptive therapy of cytomegalovirus (CMV) infections. However, even when administered at the dose specified in the package insert, there is significant interindividual variability in the plasma concentrations of ganciclovir (GCV). In addition, correlations have been reported between the area under the concentration–time curve and therapeutic efficacy or adverse events. Therefore, therapeutic drug monitoring (TDM) can be used to improve the efficacy and safety of preemptive VGCV therapy.

**Objective:**

This study aims to evaluate whether the dosage adjustment of VGCV based on TDM in patients undergoing preemptive therapy for CMV infections is associated with the successful completion rate of treatment without severe hematological adverse effects.

**Methods:**

This phase II, single-center, single-arm trial aims to enroll 40 patients admitted at the Department of Rheumatology and Clinical Immunology, Kobe University Hospital, who will receive oral VGCV as preemptive therapy for CMV infections. Participants will begin treatment with VGCV at the dose recommended in the package insert, with subsequent dose adjustments based on weekly TDM results. The primary end point will be the proportion of patients who achieve CMV antigenemia negativity within 3 weeks without severe hematological adverse events. The secondary end points will include weekly changes in CMV antigen levels, total VGCV dose, and duration of preemptive therapy. For safety evaluation, the occurrence, type, and severity of VGCV-related adverse events will be analyzed. Additionally, this study will explore the correlations between the efficacy and safety of preemptive therapy and the pharmacokinetic parameters of GCV, CMV-polymerase chain reaction values, and nudix hydrolase 15 (*NUDT15*) genetic polymorphisms. The correlation between GCV plasma concentrations obtained from regular venous blood and blood concentrations will be examined using dried blood spots.

**Results:**

This study began with patient recruitment in September 2024, with 5 participants enrolled as of June 16, 2025. The target enrollment is 40 participants, and the anticipated study completion is set for July 2027.

**Conclusions:**

This is the first study to investigate the impact of TDM intervention in patients receiving VGCV as preemptive therapy. The findings are postulated to provide valuable evidence regarding the utility of TDM in patients receiving VGCV as preemptive therapy.

**Trial Registration:**

Japan Registry of Clinical Trials jRCTs051240080; https://jrct.mhlw.go.jp/latest-detail/jRCTs051240080

**International Registered Report Identifier (IRRID):**

DERR1-10.2196/72549

## Introduction

### Background

Cytomegalovirus (CMV) establishes a latent infection after the resolution of acute infection. Its reactivation can occur in patients undergoing immunosuppressive therapy, leading to organ-specific infections such as febrile illness, pneumonia, and retinitis [1]. For patients at high risk of CMV infection, their viral load is regularly monitored. Preemptive therapy is initiated once the viral load becomes detectable, even in the absence of symptoms. Preemptive therapy is effective in preventing the onset of CMV infection and is recommended for patients undergoing hematopoietic stem cell transplant [2-4].

Valganciclovir (VGCV) is the first-line treatment not only for the prevention and treatment of CMV infections but also for preemptive therapy. It is rapidly metabolized to its active metabolite ganciclovir (GCV). Because GCV is primarily excreted by the kidneys, the dose of VGCV is adjusted based on renal function [5]. In patients who have undergone solid organ transplant, a correlation has been reported between the therapeutic effect of GCV on CMV viremia and the area under the concentration–time curve (AUC) [6]. Therefore, sufficient AUC exposure is necessary for adequate treatment. Additionally, the relationship between AUC and adverse effects has been reported [6-9]. These reports suggest that the effective range of GCV is between 40 and 60 μg·h/mL of AUC. However, a significant interindividual variability has been observed in the plasma concentrations of GCV, even when administering the dose specified in the package insert [6,10]. To this end, dosage adjustments based solely on the package insert are insufficient, and the usefulness of therapeutic drug monitoring (TDM) for GCV has been reported [7]. However, the utility of routine GCV concentration measurements and TDM remains controversial and is not currently being conducted [11].

Recently, dried blood spot (DBS) sampling, which involves collecting a small amount of blood from the fingertip onto a filter paper, has been increasingly performed in clinical practice as a less invasive method to facilitate TDM [12,13]. In addition, nudix hydrolase 15 *(NUDT15*) polymorphisms were reported to influence the antiviral efficacy and cytotoxicity of GCV [14]. However, the clinical utility of DBS and measuring *NUDT15* polymorphisms for VGCV treatment has not yet been established.

### Study Objectives

The primary objective of this study is to evaluate whether the dosage adjustment of VGCV based on TDM in patients undergoing preemptive therapy for CMV is associated with the completion ratio of treatment without adverse hematological effects. Additionally, this study aims to investigate whether dosage adjustments based on TDM can reduce the time required for CMV pp65 negativity or the incidence rate of adverse effects. Factors related to the pharmacokinetics of GCV and the efficacy and safety of preemptive therapy with VGCV will also be investigated. Further, this study will explore the relationship between GCV plasma concentrations obtained from venous blood and DBS whole blood concentrations at each measurement point and the relationship between *NUDT15* genetic polymorphisms and adverse events. Moreover, an exploratory analysis will be conducted to determine the relationship between CMV antigen quantification using CMV pp65 and CMV viral load measured by quantitative CMV DNA polymerase chain reaction (PCR).

## Methods

### Study Design and Study Location

This is a phase II, single-center, single-arm interventional trial. A flowchart of the study design is shown in Figure 1. This study is being conducted at Kobe University Hospital.

**Figure 1 figure1:**
[figure not shown]
Flowchart of the study design. CMV: cytomegalovirus; VGCV: valganciclovir.

### Inclusion and Exclusion Criteria

The inclusion and exclusion criteria are presented in Textbox 1. Patients who meet inclusion criteria 1-6 will be asked by their attending physician to provide informed consent for trial participation. When the weekly measured CMV pp65 levels meet inclusion criterion 7, patients who provide written informed consent will be enrolled in this trial after confirming that they have not withdrawn their consent and still meet all the criteria.

Study inclusion and exclusion criteria.
**Inclusion criteria**
Inpatients at the Department of Rheumatology and Clinical ImmunologyTreated with prednisolone more than or equal to 0.5 mg/kg with/without immunosuppressive agents as initial therapyAged 18 years or older at the time of consentWritten informed consent has been obtained regarding their voluntary participation in this clinical studyNo symptoms due to cytomegalovirus (CMV) infection (eg, fever, cough, dyspnea, abdominal pain, diarrhea, bloody stools, dysopsia)Not received valganciclovir (VGCV) therapy for at least 2 weeks before starting this clinical studyTest positive for CMV pp65 antigen and meet one of the following conditions: (1) CMV pp65 antigen is more than or equal to 10 per 2 slides or (2) CMV pp65 antigen is more than or equal to 1 per 2 slides and less than or equal to 9 per 2 slides, and the retest result after 2 to 8 days is that CMV pp65 antigen is more than or equal to 5 per 2 slides and higher than the initial value.
**Exclusion criteria**
Patients undergoing dialysisSignificant bone marrow suppression such as neutrophil count less than 500/mm^3^ or platelet count less than 25,000/mm^3^Pregnancy or possible pregnancyKnown allergies or drug sensitivities to VGCV, ganciclovir, acyclovir, or valacyclovirHemoglobin levels less than 8.0 g/dLTaking probenecidThe investigator deems inappropriate

### Intervention

The study schedule is presented in Table 1. Patients will receive VGCV orally at the dosage specified in the package insert, based on creatinine clearance (Ccr) calculated using the Cockcroft-Gault equation [15]. On day 3 following the initiation of VGCV therapy, venous blood samples will be collected before and 2 hours after the morning dose of VGCV. The plasma concentrations will be measured using liquid chromatography-tandem mass spectrometry [16].

**Table 1 table1:** Summary of the study schedule.

		Hospitalization	Preobservation period	Treatment period									Closeout		Postobservation period
				Week 1					Weeks 2-3						
				Day 1	Day 3	Day 4	Day 5	Day 1		Day 2	Day 3				
**Enrollment**															
	Eligibility screening	✓	✓	✓											
	Informed consent	✓													
	Registration			✓											
**Intervention**															
	Blood sampling for TDM^a^				✓			✓							
	TDM					✓				✓					
	Dose adjustment						✓				✓				
	Blood sampling for *NUDT15*^b^ genotyping											✓			

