Protocol treatment will continue for at least 2 weeks up to a maximum of 3 weeks from the day of VGCV initiation until CMV pp65 is confirmed to be negative. If CMV pp65 is not confirmed to be negative at 3 weeks after the initiation of VGCV, posttreatment will be performed at the discretion of the physician. Additionally, DBS sampling will be conducted 2 hours after VGCV morning dose and before each meal on day 3 after VGCV initiation to investigate the correlation between DBS-derived whole blood concentrations and plasma concentrations. Finger-prick blood will be collected onto filter papers (Whatman 903 Protein saver card), and blood collection will be conducted to ensure a sampling diameter of at least 6 mm. Genetic polymorphisms of *NUDT15* will also be analyzed using blood samples collected in this study. DNA will be extracted from blood samples, and *NUDT15* polymorphisms in c.415C>T; rs116855232 (p.R139C) and c.416G>A; rs147390019 (p.R139H) will be genotyped using a TaqMan genotyping assay (ID: C_154823200_10 and C_162697298_10). The postobservation period will be 2 weeks after the completion of VGCV administration to assess adverse events and relapse of CMV infection.

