### Sample Size Calculation

A preliminary survey was conducted among 20 patients admitted to the Department of Rheumatology and Clinical Immunology at our hospital between January 2020 and August 2022. The proportion of patients who were unable to complete treatment with hematological toxicities was 65% (13/20). None of the patients failed to complete the treatment because of nonhematological adverse events. The proportion of patients who could not complete treatment for reasons other than adverse events was 5% (1/20). Except for the above cases, none of the other patients failed to become CMV pp65–negative within 3 weeks. Approximately 30% of the patients achieved CMV pp65 negativity within 3 weeks without severe hematologic adverse events. The incidence of hematologic toxicities when GCV AUC was maintained at 40-60 μg·h/mL by TDM was estimated to be 36.5%, based on a previous report [9]. Assuming that the rate of treatment incompletion due to reasons other than adverse events or the rate of failure to achieve CMV pp65 negativity within 3 weeks remained at 5%, the estimated rate of patients who would fail to complete treatment owing to adverse events or fail to achieve CMV pp65 negativity within 3 weeks of TDM would be 41.5%. Therefore, the proportion of patients expected to achieve CMV pp65 negativity within 3 weeks without adverse events under TDM was assumed to be 58.5%. Under conditions of a 2-sided significance level of 5% and a power of 80%, the required sample size to detect an increase in the proportion of patients completing treatment without adverse events was determined to be 31. Considering potential dropouts, the sample size was set at 40.

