#### Exploratory Analysis

The median (or mean) of the estimated AUC and dose-adjusted estimated AUC will be calculated for each renal function at the start of treatment (Ccr≤30, 30<Ccr≤60, 60<Ccr≤80, Ccr>80 mL/min). Kruskal-Wallis and Dunn multiple comparisons tests will be performed for each group. A correlation analysis will be conducted between Ccr and the recommended probable dose by using Bayesian estimation. Single and multiple regression analyses with the dose-adjusted estimated AUC as the objective variable and clinical information as the explanatory variables will be performed to explore the factors affecting the dose-adjusted estimated AUC. The proportion of CMV antigen-positive cells that disappear in less than 3 weeks of treatment will be calculated, and a binomial test will be performed against the proportions in the preliminary study. The patients will be grouped according to the presence or absence of disease or CMV infection recurrence, and the median (or mean) of the estimated trough blood concentration, estimated AUC, and total exposure will be calculated in each group. If necessary, the Mann-Whitney *U* test will be performed. The actual total dose of VGCV during the preemptive therapy and the total dose assuming that VGCV is administered at the dose stated in the package insert will be calculated, and a Wilcoxon signed-rank test will be performed. Patients will be grouped according to *NUDT15* genotype (wild-type, homozygous variant or heterozygous variant), and the number and proportion of adverse events in each group will be calculated. Fisher exact test will be performed. Additionally, the median (or mean) estimated trough plasma concentration, estimated AUC, and total exposure will be calculated for each group, and a Mann-Whitney *U* test will be conducted. If both CMV pp65 antigen and CMV-PCR are positive, the correlation will be analyzed using the Spearman rank correlation coefficient. *P* values calculated from the above analyses will be used as references.

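### The only NUDT15 blood sample is scheduled at closeout although usable blood is drawn from day 1, so genotypes could be lost in patients who stop early for toxicity (minor, exploratory analysis only)

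*Protocol article*

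**What the plan says.** Table 1 (Methods, Intervention) gives "Blood sampling for *NUDT15*^b^ genotyping" a row of its own with a single tick. The column headers are displaced in the extracted text, so the visit has to be read from the other rows; that reading gives closeout (see the check below). The text under Estimated Apparent Clearance names no visit: "Genetic polymorphisms of *NUDT15* will also be analyzed using blood samples collected in this study".

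Blood is available well before closeout. Table 1 ticks laboratory data on day 1 and day 3, and the Intervention section adds: "On day 3 following the initiation of VGCV therapy, venous blood samples will be collected before and 2 hours after the morning dose of VGCV". Closeout comes much later, because "Protocol treatment will continue for at least 2 weeks up to a maximum of 3 weeks from the day of VGCV initiation".

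The genotype is used in the Exploratory Analysis section: "Patients will be grouped according to *NUDT15* genotype (wild-type, homozygous variant or heterozygous variant), and the number and proportion of adverse events in each group". The plan applies Fisher's exact test to these counts. Estimated trough, AUC and total exposure are also compared between genotype groups. P values from that section are for reference only.

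**The concern.** The analysis relates a fixed baseline characteristic to toxicity during treatment, but that characteristic is recorded only when treatment ends. If attendance at closeout depends on how treatment went, then whether a genotype is available depends on the outcome. The patients most exposed to this are those who stop early because of cytopenia, and they are the adverse-event cases in the Fisher table.

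At stake are the adverse-event proportions by genotype, the power of a test that is already weak at 40 patients, and the number of patients in the genotype comparison of AUC, trough and exposure. The article states in its Discussion that no human studies of NUDT15 and ganciclovir exist yet, so the proportions reported here may be the first that readers see.

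**Working it through.** **1. Which visit the tick belongs to.** The adverse-event row of Table 1 has nine ticks for nine visits: week 1 days 1, 3, 4 and 5; weeks 2-3 days 1, 2 and 3; closeout; postobservation. The NUDT15 tick is in the same column as the eighth of these. It also shares a column with the next-to-last tick for CMV pp65/PCR and for laboratory data. That column is closeout.

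**2. How many genotypes could be at risk.** Sample Size Calculation assumes 36.5% haematological toxicity under monitoring: 40 × 0.365 = 14.6, about 15 patients. At the preliminary survey's 65% (13/20) it would be 40 × 0.65 = 26. These are upper limits, reached only if every patient with toxicity misses closeout, which the article does not say. With a day 1 or day 3 sample, no genotype depends on a closeout visit.

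**3. What loss does if it depends on toxicity alone.** Let p be the true toxicity risk in a genotype group and f the fraction of toxicity cases without a genotype. The observed proportion is p(1 − f)/(1 − pf). The observed odds are p(1 − f)/(1 − p), so the factor (1 − f) cancels from the odds ratio.

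Assumptions not in the documents: 20% carriers, true odds ratio 5, f = 0.5. With overall toxicity held at 36.5%, the risks are 0.670 in carriers and 0.289 in wild type (0.2 × 0.670 + 0.8 × 0.289 = 0.365).

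- Carriers: 0.670 × 0.5/(1 − 0.670 × 0.5) = 0.335/0.665 = 0.504.
- Wild type: 0.289 × 0.5/(1 − 0.289 × 0.5) = 0.1445/0.8555 = 0.169.
- Odds ratio: (0.504/0.496)/(0.169/0.831) = 5.0, unchanged.
- Simulated power of Fisher's test, 40 patients enrolled: about 0.43 with no loss, 0.31 with this loss.
- Range: at 10% carriers power goes from about 0.23 to 0.16; at 30%, from about 0.54 to 0.37.
- With a true odds ratio of 1, the rejection rate was at most 0.033 in every scenario, so type I error is not inflated.

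**4. What loss does if it is also heavier in carriers.** With 50% of toxicity cases lost among carriers and 25% among wild type (20% carriers, odds ratio 5), the observed odds ratio is 5.0 × 0.50/0.75 = 3.3 and power is about 0.19.

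**5. The same contrast in one illustrative table.** Take 6/8 carriers and 9/32 wild type with adverse events (assumed).

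| Genotypes lost | Carriers | Wild type | Odds ratio | Fisher P |
|---|---|---|---|---|
| None | 6/8 | 9/32 | (6 × 23)/(2 × 9) = 7.67 | 0.036 |
| One third of cases in both groups | 4/6 | 6/29 | (4 × 23)/(2 × 6) = 7.67 | 0.043 |
| One third of cases in carriers only | 4/6 | 9/32 | (4 × 23)/(2 × 9) = 5.11 | 0.15 |

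The large change in P appears only in the last row, where loss is confined to carriers.

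**The case against.** The strongest reply is that stopping treatment is not leaving the study. The survey's 65% is failure to complete treatment, not loss to follow-up. Nothing restricts closeout to completers; a patient who stops early may have closeout at that point, patients are inpatients at enrolment, and laboratory blood is taken again at postobservation. How early stoppers are handled is detail that an article may leave to the full protocol. The text would also allow genotyping from earlier study blood. All of this stands: selective loss is possible but not established. It does not remove the point, because the only scheduled sample is still at closeout and the article keeps no earlier aliquot.

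Two stronger readings are tempting. One is that sampling after the toxicity is itself a fault. It is not: germline genotype does not change with treatment, so timing matters only through missing samples. The other is that losing toxicity cases biases the genotype-toxicity association toward the null. Steps 3 to 5 show that this holds for the odds ratio only if carriers with toxicity are lost more often than other patients with toxicity, and nothing in the documents supports that.

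It is also fair to say that little depends on this analysis. It is exploratory, and genotype enters neither the dose adjustment nor the primary test.

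**Conclusion.** The point holds as a minor design weakness. The only scheduled NUDT15 sample is at closeout, with no visible benefit, although blood is drawn from day 1. If early stoppers miss closeout, adverse-event proportions by genotype come out too low (67% read as 50% in carriers and 29% as 17% in wild type, with half of the toxicity genotypes lost) and power falls from about 0.43 to 0.31. The odds ratio and the type I error are unaffected unless loss also depends on genotype.

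These sizes rest on an assumed 20% carrier frequency, an assumed odds ratio of 5, assumed loss fractions, and the plan's own 36.5% toxicity rate. The location of the tick rests on the alignment of rows in an extracted table. The primary end point is not affected.

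**What to change.** In Table 1, move the NUDT15 tick from closeout to day 1 (after registration) or to the day 3 draw, taking the DNA aliquot from the venous blood already collected. Keep closeout as a back-up if the early aliquot fails. Name the visit in the sentence on NUDT15 analysis so that text and table agree. In the report, give the number of missing genotypes by adverse-event status.

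No extra visit or venepuncture is needed, and genotyping can still be batched at the end; the cost is that aliquots are stored longer. With 5 of 40 patients enrolled by 16 June 2025, a change made near that date would cover most of the cohort. As a protocol modification it needs ethics committee approval before use.

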**Assessments**															
	Patient’s background^c^		✓												
	CMV^d^ pp65/CMV-PCR^e^		✓					✓				✓		✓	
	Laboratory data^f^		✓	✓	✓	✓		✓				✓		✓	
	Adverse events			✓	✓	✓	✓	✓		✓	✓	✓		✓	
	Concomitant medication		✓	✓	✓	✓	✓	✓		✓	✓	✓		✓	

^a^TDM: therapeutic drug monitoring.

^b^*NUDT15*: nudix hydrolase 15.

^c^Including sex, age, height, weight, medical history, complications, and concomitant medications.

^d^CMV: cytomegalovirus.

^e^PCR: polymerase chain reaction.

^f^Including levels of white blood cell, neutrophil, hemoglobin, platelet, hematocrit, aspartate aminotransferase, alanine aminotransferase, albumin, blood urea nitrogen, serum creatinine, estimated glomerular filtration rate, sodium, potassium, and chloride.

### Estimated Apparent Clearance

Individual estimated apparent clearance (CL/F) will be estimated using the post hoc Bayesian analysis based on a previously reported population pharmacokinetic model [17] as follows:

CL/F=7.09*(1+Ccr/68.3) (L/h)

Vc/F=10.8 (L)

Q/F=3.96 (L/h)

Vp/F=174 (L)

Ka=0.23 (/h)

T_lag_=0.93 (h)

where Vc/F, Q/F, Vp/F, Ka, and T_lag_ are the apparent volumes of distribution in the central compartment, apparent intercompartmental clearance, apparent volume of distribution in the peripheral compartment, absorption rate constant, and lag time, respectively. Additionally, interindividual variabilities of CL/F, Vc/F, Q/F, and Vp/F are 27.2, 153, 63.1, and 107%, respectively. Interindividual variabilities of Ka and T_lag_ are not included. The proportional residual variability is 42.9%. The individual AUC will be calculated using the following formula: AUC = daily dose of VGCV × (GCV molecular weight of 255.2/ VGCV molecular weight of 354.4) / estimated individual CL/F. Subsequently, the dosage will be adjusted to achieve the target AUC (40-60 μg·h/mL) by using the dose adjustment shown in Table 2. Patients will be informed of the possibility of dosing higher or lower than the package insert recommendation during the consent process. Thereafter, weekly plasma concentration measurements and dosage adjustments will be performed using the same procedure as described above, with a treatment period of up to 3 weeks. Post hoc Bayesian estimation will be performed using NONMEM version 7.5.1 (ICON).

**Table 2 table2:** Adjusted dosage of valganciclovir based on the estimated apparent clearance.

CL/F^a^ (L/h)	Adjusted dose
2.7^b^ < CL/F ≤ 4.1	450 mg once daily every other day
4.1 < CL/F ≤ 5.4	450 mg once daily for 2 days and 1 day off
5.4 < CL/F ≤ 8.1	450 mg once daily
8.1 < CL/F ≤ 12.2	450 mg twice daily and 450 mg once daily alternately
12.2 < CL/F ≤ 16.2	450 mg twice daily
16.2 < CL/F ≤ 24.3	900 mg in the morning and 450 mg in the evening
24.3 < CL/F ≤ 32.4	900 mg twice daily
32.4 < CL/F ≤ 40.5	1350 mg in the morning and 900 mg in the evening
40.5 < CL/F ≤ 48.6	1350 mg twice daily

^a^CL/F: estimated apparent clearance.

^b^For patients with CL/F less than or equal to 2.7 or greater than 48.6, consider dosage individually.

Protocol treatment will continue for at least 2 weeks up to a maximum of 3 weeks from the day of VGCV initiation until CMV pp65 is confirmed to be negative. If CMV pp65 is not confirmed to be negative at 3 weeks after the initiation of VGCV, posttreatment will be performed at the discretion of the physician. Additionally, DBS sampling will be conducted 2 hours after VGCV morning dose and before each meal on day 3 after VGCV initiation to investigate the correlation between DBS-derived whole blood concentrations and plasma concentrations. Finger-prick blood will be collected onto filter papers (Whatman 903 Protein saver card), and blood collection will be conducted to ensure a sampling diameter of at least 6 mm. Genetic polymorphisms of *NUDT15* will also be analyzed using blood samples collected in this study. DNA will be extracted from blood samples, and *NUDT15* polymorphisms in c.415C>T; rs116855232 (p.R139C) and c.416G>A; rs147390019 (p.R139H) will be genotyped using a TaqMan genotyping assay (ID: C_154823200_10 and C_162697298_10). The postobservation period will be 2 weeks after the completion of VGCV administration to assess adverse events and relapse of CMV infection.

